## Abstract

**Background:**

The majority of nursing home residents with dementia experience behavioural and psychological symptoms like apathy, agitation, and anxiety. According to analyses of prescription prevalence in Germany, antipsychotic drugs are regularly prescribed as first-line treatment of neuropsychiatric symptoms in persons with dementia, although guidelines clearly prioritise non-pharmacological interventions. Frequently, antipsychotic drugs are prescribed for inappropriate reasons and for too long without regular reviewing. The use of antipsychotics is associated with adverse events like increased risk of falling, stroke, and mortality. The aim of the study is to investigate whether a person-centred care approach, successfully evaluated in nursing homes in the United Kingdom, can be implemented in German nursing homes and, in comparison with a control group, can result in a clinically relevant reduction of the proportion of residents with antipsychotic prescriptions.

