## Background

Prescription rates of antipsychotic drugs for residents in German nursing homes are considerably high [1] and have not changed for years [2–5]. Recent data show that antipsychotics are prescribed for almost 30 % of German nursing home residents [1]. Studies indicate that up to two thirds of antipsychotics for residents are prescribed for inappropriate reasons [6]. Furthermore, antipsychotics are often prescribed for too long without carrying out a regular review [7]. Both long-term and short-term use of antipsychotics increase mortality compared to non-users [8–10], with cardiac death and infections being the main causes. All antipsychotics are associated with an increased risk of stroke, and the risk might even be higher in patients/residents receiving atypical antipsychotics compared to those receiving conventional antipsychotics [11]. Adverse effects also include sedation, dizziness and increased risk of falling and fall-related injuries, tremor and rigidity [12–16], worsening of cognitive function [17], and other effects which are most likely to result in reduced quality of life (QoL) and well-being as well as withdrawal from social life and participation.

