## Trial objective

The aim of our study is to investigate whether a PCC approach, successfully evaluated in nursing homes in the United Kingdom [35], can be implemented in German nursing homes and, in comparison with a control group, can result in a clinically relevant reduction of the proportion of residents with antipsychotic prescriptions. Our *primary outcome* is the proportion of residents with at least one antipsychotic prescription (long-term medication) after 12 months of follow-up.

A further aim is to investigate whether QoL will improve or at least be unchanged as shown by Fossey et al. [35]. In accordance with the results of the primary efficacy study and a Cochrane review [33], we assume that the intervention is not only effective but also does not harm the residents, i.e. dementia-related BPSD will not worsen in the intervention group, and prescription rates of other psychotropic medication as well as the application of physical restraints will not increase. Therefore, the following *secondary outcomes* will be evaluated (at 12 months):Presence of agitated behaviour,Residents’ QoL,Median daily dose of antipsychotics in chlorpromazine equivalents,Proportion of residents with dementia with antipsychotic prescription,Proportion of residents without dementia with antipsychotic prescription,Prescription prevalence of other psychotropic drugs (antidepressants, anxiolytic and hypnotic drugs, acetyl-cholinesterase inhibitors),Safety parameters are number of falls, fall-related fractures and sutures, fall-related medical attention as well as the proportion of residents with at least one physical restraint (bilateral bedrails, belts, fixed tables, and other measures limiting free body movement), and the number and types of physical restraints.

Additionally, a health economic evaluation will be conducted alongside the study. A process evaluation will also be performed, aiming to comprehensively analyse the underlying processes as well as the barriers and facilitators of the implementation of this multicomponent intervention, giving special focus to regional differences. The programme will be implemented in nursing homes in East, North, and West Germany in order to evaluate its supra-regional generalisability.

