#### Resident level

Five measurement points are scheduled in the study: baseline assessment and measurements after 3, 6, 9, and 12 months (see Table 2).

**Table 2 Tab2:** Measurements at resident level

Point of measurement		Characteristics	Measure
t_0_	Baseline^a^	Socio-demographic and clinical data	Routine data
		Quality of life	QoL-AD
		Cognition	DSS
		Agitated behaviour	CMAI
		Medication data	Routine data
		Falls and fall-related medical attention	Routine data
		Physical restraints	Routine data
t_1_ t_2_ t_3_	3, 6, and 9 months after baseline	Medication data	Routine data
		Falls and fall-related medical attention	Routine data
		Physical restraints	Routine data
		Clinical course (emergencies, hospital admissions, change in nursing care dependency, and physician contacts)	Routine data
t_4_	12 months after baseline	Quality of life	QoL-AD
		Cognition	DSS
		Agitated behaviour	CMAI
		Medication data	Routine data
		Falls and fall-related medical attention	Routine data
		Physical restraints	Routine data
		Clinical course (emergencies, hospital admissions, change in nursing care dependency, and physician contacts)	Routine data

^a^New participants after t_0_ will be assessed with the same characteristics and measures as for baseline at the subsequent measurement point

At baseline (t_0_), socio-demographic and clinical data will be assessed from all included residents and will be documented in a case report form (CRF).

Residents’ QoL will be measured at t_0_ and t_4_ using the German version [46] of a QoL instrument which is also suitable for residents with dementia. The validated instrument *Quality of life-Alzheimer’s disease—QoL-AD* [47, 48] comprises 13 items with 4-point Likert scales for self or proxy assessment (total score ranges from 13 to 52, higher scores mean higher QoL). Self-assessment will be performed by short interviews with the residents; proxy assessment will be conducted by nursing staff.

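### Hospital admissions and emergencies are scheduled at t1 to t4 but are not safety parameters, so serious events unrelated to falls stay outside the stated safety comparison

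*Protocol article*

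**What the plan says.** In Trial objective the authors write that "we assume that the intervention is not only effective but also does not harm the residents". They spell this out as no worsening of behavioural symptoms and no increase in other psychotropic drugs or restraints. The outcome list follows directly: "Therefore, the following *secondary outcomes* will be evaluated (at 12 months"). Its last entry fixes the safety parameters: "Safety parameters are number of falls, fall-related fractures and sutures, fall-related medical attention", "as well as the proportion of residents with at least one physical restraint", and the number and types of restraints.

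Table 2 (Measures, Resident level) has a further row, "Clinical course (emergencies, hospital admissions, change in nursing care dependency, and physician contacts"), taken from routine data. It is scheduled at t1 to t3 ("3, 6, and 9 months after baseline") and again at t4, without distinction of group. It is not scheduled at baseline.

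The rationale names serious risks of the drugs. The Abstract speaks of "adverse events like increased risk of falling, stroke, and mortality", and the Background states "All antipsychotics are associated with an increased risk of stroke". The Background also says that antipsychotics raise mortality, mainly through cardiac death and infections.

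**The concern.** The outcome list is presented as the means of evaluating the no-harm assumption. Apart from events that follow a fall, it contains no serious medical event. Data on such events are nevertheless due to be gathered at every follow-up visit.

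If admissions or emergencies rose in the intervention group after prescriptions changed, nothing in the stated safety comparison would show it. If they fell, the report would omit a result that bears on the trial's rationale. The article itself fixes the list of secondary outcomes, so this is not an analysis detail left to a supplementary file.

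**Working it through.** **1. Where each kind of event appears.**

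| Place in the article | Falls and consequences | Restraints | Admissions, emergencies |
|---|---|---|---|
| Abstract, Methods/design | named as safety | not named | not named |
| Trial objective, outcome list | named as safety | named as safety | not named |
| Resident level, safety paragraph | named as safety | named as safety | not named |
| Table 2, t1 to t4 | collected | collected | collected |
| Statistical analysis | as secondary outcomes | as secondary outcomes | no analysis stated |

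Admissions and emergencies are collected at 4 of the 5 measurement points and compared at none in the text shown.

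**2. Whether another outcome would catch them.** The CMAI is taken only at t0 and t4, looks back two weeks, and is obtained by interviewing nursing staff, who cannot be blinded. The outcome list is evaluated at 12 months, and the Sample size section says the analyses focus on residents living in the homes at that point. A resident in behavioural crisis at month 4 who is admitted and then dies or moves contributes no 12-month CMAI score. The admission record would show the event.

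**3. How many residents leave.** The Sample size section expects 25 % early termination from death or moving.
- 36 homes: 36 × 65 = 2340, and 0.25 × 2340 = 585.
- 30 homes, if six drop out: 30 × 65 = 1950, and 0.25 × 1950 ≈ 488.

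These are residents leaving the baseline population, not events.

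**4. New residents.** For those entering after t0, the article schedules retrospective capture since entry only for medication data and safety parameters. The footnote to Table 2 gives them the baseline set, which has no clinical-course row. Admissions between entry and the first measurement are therefore not scheduled, because admissions are not classed as a safety parameter.

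**5. What a comparison could show.** The plan's own figure comes first.
- Inputs: 26 % v 14 %, two-sided α = 0.05, 90 % power, ICC 0.05, 65 residents per home.
- n = [1.960·√(2·0.20·0.80) + 1.282·√(0.26·0.74 + 0.14·0.86)]² / 0.12² ≈ 232 per group.
- Design effect = 1 + 64 × 0.05 = 4.2; 232 × 4.2 = 974.4; 974.4 / 65 = 14.99, so 15 homes per group. The stated figure reproduces.

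For the 12-month proportion of residents with at least one admission, the article gives neither a rate nor an ICC. **Assumed:** control proportion p from 20 to 50 %, ICC from 0.01 to 0.05, 15 to 18 homes of 65 per group.
- Effective size per group: n_eff = 65k / (1 + 64·ICC). CI half-width ≈ 1.96·√(2p(1−p)/n_eff).
- Best case (p = 20 %, ICC 0.01, k = 18): n_eff = 1170/1.64 = 713.4; half-width 4.2 points.
- Worst case (p = 50 %, ICC 0.05, k = 15): n_eff = 975/4.2 = 232.1; half-width 9.1 points.
- Increase detectable with 80 % power (two-sided 5 %): from 6.3 points (p = 20 %, ICC 0.01, k = 18) to 13.0 points (p = 40 %, ICC 0.05, k = 15).

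**The case against.** The other side has real points.

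- *The stated meaning of harm is covered.* The article defines harm by behavioural symptoms, other psychotropics and restraints, and each has a matching outcome (agitation standing for the first). A behavioural deterioration is not wholly invisible. This stands, but it leaves serious medical events out of an evaluation the article itself sets up.
- *Additional files 1 and 2 may use the data.* Clinical-course items are plausible inputs to the health economic evaluation, and the statistical supplement is not shown. It would be wrong to say the data are never used. A cost input is still not a safety comparison between groups, and the outcome list is fixed here.
- *Serious or unexpected events go to the ethics committees.* They do, but that is notification, and no comparison by group is stated.
- *The list may be open.* The Abstract and the Resident level section word it as examples. Trial objective does not.
- *Power is limited.* The planned contrast in prescribing is 12 points. If antipsychotics doubled an admission probability of 20 to 40 % in non-users (an assumption), the groups would differ by 0.12 × 20 to 40 % = 2.4 to 4.8 points, below the 6 to 13 points detectable. This stands: the added comparison would probably not demonstrate a benefit of that size.

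A reader might also infer that falling is the only named risk compared. That is not so: fall-related injuries and quality of life are outcomes too. Nor does the Background list cardiac events and infections as separate morbidity risks. It gives cardiac death and infections as causes of the excess mortality.

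**Conclusion.** The point holds as a gap in outcome coverage. The safety parameters comprise falls, their consequences and restraints. Admissions and emergencies are scheduled at t1 to t4 but enter no between-group comparison stated in the article. The consequence is sharpest for residents who die or move before t4.

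It goes no further than that. The no-harm statement is an assumption examined by exploratory outcomes, not a confirmatory conclusion. The primary result and the sample size are untouched. A reader might want a number of uncompared admissions, but the document gives no rate and none is claimed. The precision of about 4 to 9 points rests on the assumed proportions and ICC above, treats admission as one yes/no outcome per resident, and takes every home as contributing 65 residents. The claim itself needs none of these assumptions.

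**What to change.** In Trial objective, add hospital admissions and emergencies to the safety parameters. State that they are compared by group as rates per resident-time, from t0 (or entry, for new residents) to t4, death or departure, with cluster-adjusted 95 % confidence intervals, and interpreted exploratively. In Resident level, state the look-back for these items. It is given as the last three months for falls and restraints but not for clinical course. Classing them as safety parameters also brings new residents' admissions since entry into the retrospective capture already planned.

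Cost: one more exploratory comparison, with little power for modest differences, and slightly more retrospective extraction, including dates of death or departure if these are not already recorded. Visits and sample size do not change. Table 2 has no clinical-course row at baseline, so the comparison could not be adjusted for earlier admissions from the listed data. A field for the reason for admission would be useful but is new data collection and optional. Only the pilot phase is reported as started, so the change is still practicable.

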## Methods/design

### Study design

The study is a multicentre, cluster-randomised controlled, pragmatic trial using parallel groups with a 1:1 randomisation (on cluster level) and 12 months of follow-up. Figure 1 displays the study flow.

**Fig. 1 Fig1:**
[figure not shown]
Flow chart of EPCentCare

The optimised usual care for both study groups will be a medication review by an experienced geriatrician and/or psychiatrist with feedback to the prescribing physician. All the general practitioners (GPs), neurologists, and psychiatrists for the study participants will be offered 2 h of continuing medical education on the subject.

For the nursing homes in the intervention group, an educational intervention on PCC and a continuous supervision programme will be conducted. The control group will receive no further intervention other than the optimised usual care.

### Participants and recruitment

#### Inclusion and exclusion criteria

The study will be performed in 36 nursing homes in the cities/catchment areas of Halle (Saale), Lübeck, and Witten. Individual nursing homes or units working independently within a large nursing home will be defined as a cluster.

Inclusion criteria will be nursing homes with at least 50 residents; each participating institution must have sufficient resources (staff, time) to conduct the study, and no special “dementia projects” or other activities potentially influencing the intervention will be allowed.

All residents within a cluster will be eligible to participate in the study. Exclusion criteria at the individual level will be:Temporary stay in respite care and/orPrimary diagnosis of schizophrenia, or bipolar disorder.

#### Recruitment of study centres and study participants

In each study region, nursing homes will be randomly selected from the respective nursing home register. These facilities will be invited to take part in the study either via postal mail or telephone. The study will be presented to the directors of the nursing homes, who will decide whether their home will participate. A resident representative or, if not available, a residents’ advocate will be involved in all activities and decisions.

All eligible residents or their proxies or legal guardians will receive oral and written information about the aims and purpose of the study as well as all the information required according to good clinical practice (GCP) rules to create informed consent. Questions and additional information about the study will be available from the project staff of the respective study centre, either in person or by phone. Consent may be withdrawn for any reason at any time and without notice, without incurring any disadvantages for the residents. All residents who move into the nursing home during the study period will be eligible to participate too and will be asked for consent.

A total of four nursing homes (two facilities each in the intervention group and in the control group) will take part in a controlled pilot study at the study centre in Halle (Saale). The study will be implemented respectively in recruiting phases of four nursing homes per study site with a time shift of 2 months. The data collection will end in the last quarter of 2016.

### The EPCentCare intervention

The study intervention will consist of four components, depending on group assignment (see Table 1).

**Table 1 Tab1:** Components of the study intervention

	Optimised usual care		Person-centred care (PCC) approach	
	Continuing medical education [23, 36]^a^	Medication review every 3 months [23, 35, 36, 39]^a^	Information for nursing home staff	Training and support of “experts for PCC for the elderly” [25–27, 29, 35, 40–43]^a^
Control group	x	x		
Intervention group	x	x	x	x

^a^Numbers in brackets indicate references concerning the theoretical and/or empirical background of study components

#### Continuing medical education provided for prescribing physicians (intervention and control group)

In Germany, residents of nursing homes have a free choice of medical practitioner. Therefore, the continuing medical education (CME) will address all physicians who are involved in the care of the participating residents of both study groups. The GPs, neurologists, psychiatrists, and geriatricians will take part in a 2-h workshop.

Topics of the training will be diagnostics and care for people with dementia as well as non-pharmacological and pharmacological treatment options for people with BPSD. The education content will be prepared in accordance with German national evidence-based clinical practice guidelines [23, 36]. Parts of the educational material have been used successfully in former studies [37, 38]. The focus will be on psychotropic medications and antipsychotics (e.g. guideline-based recommendations for use, adverse effects/risks, and contraindications). Furthermore, we will present and discuss options for optimising treatment and care for people with BPSD in nursing homes using the example of EPCentCare. All participants will receive written information about the central aspects of the training.

Physicians who do not attend the workshop, as well as new physicians joining the project during the study period, will receive written information on the workshop topics. The workshop will be offered locally at the participating universities.

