#### Training and support of “experts for person-centred care for the elderly—EPA” (only intervention group)

Based on Fossey et al. [35, 40], selected staff from the nursing homes in the intervention group will be trained and instructed to work as “experts for person-centred care (PCC) for the elderly (EPA)”. The responsibilities of the EPA will be:Identifying organisational needs for change within the institution and opportunities for developing specific aspects of carePlanning and supporting the implementation of PCC in the nursing facility.Initiating discussions with colleagues about PCC activities for specific residents.Discussion with colleagues about the medication review or contacting the prescribing physician.Advice and support of colleagues as facilitator and primary contact person for colleagues, relatives, and physicians.

The training programme for the EPA will include a 2-day initial workshop on PCC as well as continuous training and support over the 12-month study period.

The workshop will take place on two consecutive days at the respective study centre/university. An expert in PCC will present the following content:Introduction to EPCentCare.Antipsychotics in people with BPSD: list of medications, reasons for prescription, side effects, and guideline-based recommendations for use [23, 36, 41].PCC on resident level: according to Kitwood [26, 27], recognising individual residents’ needs and reasons for behaviour [40], dealing with challenging behaviour [25, 29, 40, 42, 43], and reflection of case examples.PCC on institutional level: assessing, supporting, and managing development of PCC in a nursing home [40, 41].Supervision/support programme [35].

The trained experts will be supported during the intervention period by a study nurse specialised in dementia and PCC (continuous in-house training). The supervision may be carried out individually and/or in groups in a minimum time frame of 3 to a maximum of 6 h per month and nursing home. As part of the supervision, the EPA will be supported in recognising residents’ needs [40] in implementing PCC plans, in promoting the participation of the residents in activities, and possibly in implementing environmental changes.

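### A plausible contamination path through physicians who treat residents in both arms is neither limited nor measured

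*Protocol article*

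**What the plan says.** All references are to the protocol article.

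- **Outcome and unit of randomisation.** The primary outcome is the proportion of residents with at least one antipsychotic prescription at 12 months (Trial objective). Clusters are homes, or independently working units of one large home, in three cities or catchment areas (Inclusion and exclusion criteria). Randomisation is stratified by region and recruiting phase, with four homes per stratum (Cluster-randomisation).
- **Physicians.** "In Germany, residents of nursing homes have a free choice of medical practitioner". For that reason the medical education "will address all physicians who are involved in the care of the participating residents of both study groups" (Continuing medical education).
- **Workshop content.** It follows national guidelines: "The focus will be on psychotropic medications and antipsychotics". In addition, "we will present and discuss options for optimising treatment and care for people with BPSD in nursing homes using the example of EPCentCare". Participants receive written information on the central aspects; physicians who do not attend receive it on the workshop topics.
- **Experts in intervention homes.** Their listed responsibilities include "Discussion with colleagues about the medication review or contacting the prescribing physician" and "Advice and support of colleagues as facilitator and primary contact person for colleagues, relatives, and physicians" (Training and support of experts for person-centred care).
- **Control condition.** "The control group will receive no further intervention other than the optimised usual care" (Study design). Table 1 counts the medical education and the medication review as that care.
- **Physician identity.** The prescribing physician appears in Table 3, among the data for medication reviews of residents on an antipsychotic. Table 2 lists physician contacts, but no physician identity for other residents.

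**The concern.** Randomising homes separates the nursing staff of the two arms but not the prescribers. A physician with residents in an intervention home and in a control home belongs to both arms, and that physician's decisions form the endpoint.

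Two routes could move intervention content to control residents:

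1. **The workshop example.** The section headed The EPCentCare intervention uses that name for all four components, two of which are for intervention homes only. Nothing confines the example to the other two, so physicians of control residents may be shown the person-centred programme as a model of good care.
2. **Expert contact.** A shared physician who discusses deprescribing with an expert in an intervention home may act on it for control residents too.

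Either route would lower control prescribing and narrow the contrast on which the trial is powered. If overlap is not recorded for all residents, a small or null difference is harder to interpret: a weak programme and a diluted comparison could look alike. Restricting a check to residents listed in Table 3 would not help, because it would select on antipsychotic use, which is the outcome variable.

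**Working it through.** **Inputs** (Sample size calculation): control 26% at 12 months, difference 12 points, so intervention 14%; two-sided α = 0.05; intra-class correlation 0.05; 65 residents per cluster; 15 clusters per group; 90% power; 36 clusters recruited to allow for six dropouts, i.e. 18 per group.

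**Step 1. Reproduce the plan's figure.**
- Design effect = 1 + (65 − 1) × 0.05 = 4.2.
- The pooled-variance formula for two proportions, 26% against 14%, gives 232 per group without clustering.
- 232 × 4.2 = 974.4; 974.4 / 65 = 14.99, i.e. 15 clusters per group, as stated.
- (30 + 6) × 65 = 2340 residents, as stated.

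**Step 2. Power formula.** Effective n per group = k × 65 / 4.2, which is 232.1 for k = 15 and 278.6 for k = 18. With d the difference and p̄ the mean of the two proportions p₁ and p₂:

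Power = Φ[(d − 1.96 × √(2p̄(1 − p̄)/n)) / √((p₁(1 − p₁) + p₂(1 − p₂))/n)]

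Without carry-over, d = 0.12 gives 90.1% at k = 15 and 94.5% at k = 18.

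**Step 3. Carry-over.** Let c be the share of the 12-point contrast that reaches the control arm. Control prevalence becomes 26 − 12c and the difference 12(1 − c) points. The protocol gives no value for c, so these are assumptions:

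| c | Control | Difference | Power, 15 per group | Power, 18 per group |
|---|---|---|---|---|
| 0 | 26.0% | 12.0 points | 90% | 95% |
| 10% | 24.8% | 10.8 points | 84% | 90% |
| 15% | 24.2% | 10.2 points | 80% | 87% |
| 25% | 23.0% | 9.0 points | 71% | 78% |

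Worked example, c = 10%, k = 15: p̄ = 0.194; the two standard errors are 0.0367 and 0.0364; (0.108 − 1.96 × 0.0367) / 0.0364 = 0.99; Φ(0.99) = 0.84.

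**Step 4. What c could mean.** For expert contact, c = s × f, where s is the share of control residents whose physician also serves an intervention home and f the fraction of the effect carried over. With f = 0.5, s = 0.2, 0.3 and 0.5 give the three rows. This product does not describe the workshop route, which reaches control physicians whether shared or not; nothing in the protocol allows an estimate for that route.

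**The case against.** The strongest reply is that the workshop is the comparator. It is openly part of optimised usual care, goes to both arms, and the expected control fall from 30% to 26% is attributed to that care. A workshop effect on controls is therefore intended and at least partly counted. This stands: the workshop does not contradict the statement on the control condition, and its guideline content is not contamination.

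It is also true that EPCentCare is one example in a drug-focused workshop, and that the name covers the common components too. The text permits, but does not state, that the intervention-only parts are presented. That the material for non-attenders contains the example is likewise inference.

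A reader might infer that physicians carry the intervention into the control arm. The documents do not support that. Staff information, expert training and monthly supervision stay in intervention homes; a physician can take a prescribing attitude elsewhere, not those components. Neither overlap nor carry-over is reported.

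A reader might also infer that dilution could never be detected and that a null result would be unreadable. That goes too far. Physicians must be identified to be invited, Table 3 is not the whole case report form, and the detailed analysis description and process-evaluation protocol are not shown.

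What remains is that the article describes no step to limit prescriber overlap, leaves the scope of the example open, and makes no separate allowance for either route in the 26%.

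**Conclusion.** The point holds as a plausible, unquantified and unaddressed risk. Shared prescribers are likely enough, given free choice of physician and recruitment within one catchment area, to be worth measuring. The direction is known: carry-over would bias towards no difference and could not create a false benefit.

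The size is not known. The power losses rest on assumed carry-over and on the plan's own intra-class correlation and cluster size. The 15-home column also supposes that all six allowed dropouts occur. With all 36 homes retained, 10% carry-over still leaves about 90% power, but only by using up the dropout reserve. This is a cheap improvement that protects the contrast and helps in reading a null result; it does not make the trial invalid.

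**What to change.** 1. **Workshop.** Confine the EPCentCare example, in the workshop and its written material, to the components common to both arms until the 12-month assessment (t4) is complete in that region. Guideline content stays unchanged for all physicians.
2. **Physician ID.** Record a pseudonymous ID of the responsible physician for every participating resident at that resident's baseline (t0, or the first assessment for new residents), not only for antipsychotic users. For residents present at t0 this precedes disclosure of the allocation; for later entrants it does not, which should be noted.
3. **Reporting and analysis.** Report how many physicians, and how many residents, span both arms. Pre-specify a supportive sensitivity analysis of the primary outcome by shared versus one-arm physician. State its limits: it addresses expert contact only, because one-arm physicians were offered the same workshop, and one-arm physicians are a selected subset.

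**Cost:** one illustration withheld for a time, one case report form field, one extra analysis. Design, sample size and primary test are unchanged. The article reports only that the pilot phase has started, so most homes could still be covered.
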